#### Type of analysis and handling loss-to-follow-up

Analyses will be conducted in intention-to-treat, i.e., each patient will be analyzed in the hospital to which she will be admitted and each hospital will be analyzed in the group to which it will be assigned by the randomization. If a hospital decides to withdraw from the trial after the randomization, data collection will continue until the end of the trial, according to the commitment made by the hospital authorities at the time of inclusion. This hospital will not be excluded from the analyses.

#### Statistical analysis

For reducing contamination bias, hospitals are the units of randomization and patients are the units of analysis [64, 67]. In the primary intention-to-treat analyses, we will assess the effect of the intervention on the rate of major perinatal morbidity using the multivariable generalized-estimating-equations extension of logistic regression, with an exchangeable covariance matrix, to account for the clustering of women within hospitals [68]. Changes in the risk of major perinatal morbidity in the two study groups between the 1-year baseline (pre-intervention) period and the 2-year intervention period will be compared with the use of an adjusted odds ratio (with 95% confidence intervals) for the interaction between group (intervention vs. control) and time period (intervention vs. baseline) [64, 65]. The adjusted odds ratio for interaction will be estimated with the use of data on women who were delivered during the baseline period or the intervention period and measures the intervention effect with the difference-in-differences approach [69, 70], which is adapted for generalized-estimating equation analyses of clustered binary outcomes [65]. In each group, the change over time, from the baseline to the intervention period, will be measured by the respective odds ratio, i.e. the exponent of the difference between log odds of cesarean delivery in intervention versus baseline periods. Then, additional change over time in the intervention group, relative to the concurrent change in the control group, will be estimated by the difference between group-specific differences. The exponent of the resulting difference-in-differences in log odds provides the adjusted odds ratio, with 95% CIs, for the interaction between group (intervention vs. control) and time (intervention vs. baseline), which will be used as the main measure of the intervention effect [64, 69, 70]. Two-tailed *P* values of less than 0.05 will be considered to indicate statistical significance.

All primary analyses will include adjustments for prespecified potential maternal, perinatal and institutional risk factors associated with major perinatal morbidity [64]. To conform to the intention-to-treat approach, all eligible women who deliver at participating hospitals will be included in the analyses. For adjustment variables for which less than 1% of the data are missing, we will use random imputation (performed on the basis of the observed distributions of the imputed variable and of highly correlated covariates). Variables for which more than 1% of the data are missing will be excluded from the analyses. Randomization will be stratified by level of care in hospitals. To assess whether the intervention effect will vary according to the level of care, we will test the corresponding three-way interactions: level of care × intervention × time. Subgroup-specific intervention effects will be reported for outcomes with significant three-way interactions (two-tailed tests, with *P* value of less than 0.05 will be considered statistically significant) [69, 70].

Secondary outcomes will be analyzed by means of methods similar to those used for the primary outcome. Subgroup analyses for preterm and term birth will be also planned to take into account major neonatal morbidity related to preterm birth and not related to the mode of delivery. If the generalized-estimating- equations models do not converge, the intervention effect will be estimated with the use of multivariable logistic model, which do not account for within-hospital clustering; to correct for the resulting underestimation of the standard errors, a conservative *P* value of less than 0.001 will be used [68, 70]. All analyses will be performed with the use of SAS software, version 9.4 by an independent team whose members will be unaware of the group assignments.

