### Data collection and management

#### Data collection

Clinical data are collected independently of the intervention. Subjects will be initially screened by the medical archives department staff in every participating hospital, and then will be validated by the data collectors according to the study inclusion and exclusion criteria. Computerized data collection will be performed on-site using Dacima Clinical Suite from Dacima Software Inc. [63] The electronic case report form includes individual clinical information about the mother and the newborn, namely maternal characteristics, prenatal care, labor and delivery and maternal and neonatal complications. In-hospital data will be abstracted by trained research nurses or medical archivists from the medical records of mothers and newborns at least 3 months after delivery; data will be abstracted in the same way at both intervention and control hospitals from April 2016 to March 2017 (baseline period) and from September 2017 to August 2019 (intervention period). Data collectors will be aware of the randomization assignments but will not be involved in outcomes assessment.

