### Statistical analysis plan

#### Sample size and power calculation

The sample size was calculated to maximize statistical power while minimizing the number of clusters [64]. Sample size calculations were based on a cluster RCT design [65], stratified by level of care (community, regional or tertiary care hospitals), to detect a relative reduction of 25% in major perinatal morbidity in hospitals of the intervention group compared with those of the control group. To account for clustering by hospital, we assumed an intraclass correlation coefficient of 0.001, estimated from the QUARISMA Trial data, representing 70% of deliveries in Quebec in 2010–2011 [64]. We calculated that we would have to enroll 40 hospitals in the study, with an expected total of 7360 women with one prior cesarean delivery per year (22,080 women for the 1-year baseline period and the 2-year intervention period), to achieve a power of 80% to detect a 25% relative reduction with the intervention in the major perinatal morbidity rate, assuming a baseline rate of 4.5% for the three strata, at a two-sided alpha significance level of 0.05 [64, 66].

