#### Economic evaluation

Cost-effectiveness analyses will take the perspective of the publicly funded health care system [71]. The time horizon will capture hospital-based costs and clinical events for mothers and neonates from labour onset to a minimum of 3 months postpartum. Resource use will be identified and measured from patient charts and valued using standardised government sources, following recommended methods for costing in the Canadian context [72]. A discount rate of 5% will be applied, and results will be compared to two scenarios implementing alternative discount rates of 3% to facilitate comparisons with other jurisdictions and 0% to explore the effect of discounting [71].

The main analysis will be an ITT analysis including all trial participants. To assess intervention impact, we will model changes in a composite index of major perinatal morbidities and costs in the two study groups between the 1-year baseline period and the 2-year intervention period using adjusted regression coefficients (with 95% confidence intervals) for the interaction between group (intervention or control) and time period (intervention or baseline) [64, 70]. Costs and effects will be modeled jointly using bivariate multilevel linear models that explicitly recognize potential correlations between the bivariate outcomes (major perinatal morbidities and costs) at individual and cluster (hospital) levels [73]. Crude and adjusted statistical models will be also estimated. Crude models will include study group (intervention vs. control), time period (baseline vs. intervention) and the interaction between study groups and time period. Adjusted models will use precisely the same variables for adjustment of confounding, as the main trial. All variable definitions will be identical to those used for the main trial. To address potential heterogeneity in cost-effectiveness, analyses will be repeated for pre-specified subgroups of interest (level of care, prematurity).

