### Potential limitations of the trial

Our study could have some limitations. Since hospitals will be the unit of randomization, and the number of deliveries varies across hospitals, there could be differences in the distribution of hospital characteristics across groups at baseline. These differences will be adjusted a priori in multivariable analyses. Because of potential intra-cluster variation among hospitals, the trial results could be driven by a few hospitals. Consequently, adjusted, center-specific multivariable analyses will be also conducted to assess changes over time in the major perinatal morbidity rates in each individual hospital. Furthermore, the intervention may not be fully implemented in each intervention hospitals. Finally, because we will assess a complex, multifaceted intervention, it will not be possible to determine which of its components will be primarily responsible for any observed effect.

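### The 1% missing-data rule can delete prespecified adjustment variables that are about 99% observed, so chart completeness decides the final covariate set

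*Protocol article*

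**What the plan says.** Under Statistical analysis, the protocol article commits to covariate adjustment without exception: "All primary analyses will include adjustments for prespecified potential maternal, perinatal and institutional risk factors associated with major perinatal morbidity". The same paragraph then sets two rules for incomplete covariates. Below the threshold, "For adjustment variables for which less than 1% of the data are missing, we will use random imputation". Above it, "Variables for which more than 1% of the data are missing will be excluded from the analyses". The second sentence says only variables; in context it means the adjustment variables, and I read it so.

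Three other places bear on this:
- Potential limitations of the trial relies on adjustment for baseline differences in hospital characteristics between the groups: "These differences will be adjusted a priori in multivariable analyses".
- Economic evaluation inherits the same set: "Adjusted models will use precisely the same variables for adjustment of confounding, as the main trial".
- Data collection says that the data are abstracted "from the medical records of mothers and newborns at least 3 months after delivery", so covariate completeness depends on routine charting.

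The article shows no exemption for important variables, no imputation above 1%, and no sensitivity analysis that puts a deleted variable back.

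**The concern.** Once any listed factor passes 1% missing, the promise to adjust for the prespecified factors and the exclusion rule cannot both be kept. Which factors stay then depends on charting, not on their prognostic weight: a strong risk factor just over the line goes, and a weak one just under it stays. The article already accepts imputation just below 1%, and gives no reason why total deletion becomes the better choice just above it.

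At stake is the adjusted interaction odds ratio, which the article names as the main measure of effect. The economic models are affected too, because they take over whatever set survives. This is a rule that the article fixes, not a detail left to a later analysis plan.

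**Working it through.** **Inputs from the article.** 7360 women per year; "22,080 women for the 1-year baseline period and the 2-year intervention period"; 40 hospitals; threshold 1%; main effect measure is the group-by-period interaction odds ratio. I assume that the 1% is taken over all women in both periods, since the article names no other denominator.

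**Plan's total.** 7360 × 3 = 22,080, as stated.

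**How little triggers deletion.**
- 1% × 22,080 = 220.8, so 221 missing values delete a variable.
- Values still known: 22,080 − 221 = 21,859, or 99.0%.
- Average hospital: 22,080 / 40 = 552 women. If all other hospitals are complete, one average hospital must miss the item in 221 / 552 = 40% of its charts to delete it everywhere. If it never records the item, missingness is 552 / 22,080 = 2.5%. A hospital with fewer than 221 women cannot trigger the rule alone.
- Near the line the result is close to chance. With X ~ Binomial(22,080, q), treating missingness as independent between women, P(X > 220) is about 6% at q = 0.9%, 50% at 1.0% and 93% at 1.1%.

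**When deletion does no harm: a stable imbalance.** Assume a factor with risk ratio 2 and prevalence 25% (intervention) against 20% (control) in both periods, a control rate of 4.5% and a true risk ratio of 0.75.
- Risk without the factor: 0.045 / (1 + 0.20) = 0.0375.
- Intervention arm at baseline: 0.0375 × 1.25 = 0.046875. In the intervention period: × 0.75 = 0.035156. The control arm stays at 0.045.
- Interaction odds ratio with the factor omitted: (0.035156 / 0.964844) / (0.046875 / 0.953125) = 0.7409.
- With no imbalance: (0.03375 / 0.96625) / (0.045 / 0.955) = 0.7413.

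The imbalance appears in both periods and cancels.

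**When deletion does harm: a differential change.** A simulation used 22,080 women, one third of them in the baseline year, a binary factor with 8% prevalence, 1.25% of its values missing at random, and a true interaction odds ratio of 0.741. Prevalence shifted only in the intervention arm in the intervention period. There were 100 replicates per row, fitted by logistic regression without clustering. All inputs except the number of women and the period split are assumptions; 0.741 is the odds ratio for a fall from 4.5% to 3.375%.

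| Odds ratio of factor | Shift (points) | Full data | Imputed | Dropped |
|---|---|---|---|---|
| 5 | 0 | 0.739 | 0.740 | 0.744 |
| 5 | +2 | 0.755 | 0.757 | 0.802 |
| 10 | +2 | 0.733 | 0.736 | 0.817 |
| 5 | −2 | 0.736 | 0.735 | 0.700 |

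The scatter in the full-data column is simulation error; the comparison is within rows. Simple random imputation stays within 0.003 of the full-data result. Dropping multiplies the estimate by 0.802 / 0.755 = 1.06, 0.817 / 0.733 = 1.11 and 0.700 / 0.736 = 0.95 in the shifted rows.

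A hand check treats the odds ratio as a risk ratio: (1 + 0.10 × 4) / (1 + 0.08 × 4) = 1.06; (1 + 0.10 × 9) / (1 + 0.08 × 9) = 1.10; (1 + 0.06 × 4) / (1 + 0.08 × 4) = 0.94. These agree closely.

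**The case against.** The best defence is that the rule is mechanical and stated in advance, depends on missingness and not on results, and is applied "by an independent team whose members will be unaware of the group assignments". The adjustment promise can be read as qualified by it. The design has other protection as well: randomization in blocks stratified by level of care, and a baseline year that is differenced out. Quality control of data provides entry checks, second review of about 5% of records, and a completeness check resolved by queries and site visits, so few variables may ever reach 1%. All of this stands, and it limits the harm. It does not justify deletion: queries cannot recover what was never charted, and a rule fixed in advance can still be a poor one.

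Several stronger readings are tempting but not supported:
- **Any imbalance between arms in a deleted factor biases the result.** A stable imbalance cancels, as shown above.
- **Covariate selection is driven by results.** The trigger is missingness, and the analysts are blinded.
- **Data on women are thrown away.** No woman leaves the analysis; only that covariate's values go unused.
- **Body mass index or another named item will probably be lost.** The article gives no missingness rates, and names body mass index only as a nomogram input.
- **Adjustment is the trial's main protection against imbalance.** The limitations section relies on it for hospital characteristics, but stratification and the baseline year also protect.
- **The perinatal covariates include variables on the causal path.** The article does not list the covariates, so this cannot be judged from it.

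**Conclusion.** The point holds as a flaw in a fixed rule. The article promises a prespecified adjustment set and then lets 221 blanks in 22,080 records remove a member of it, with nothing shown to restore it. The arithmetic of the trigger is firm, given a denominator of all women in both periods.

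The consequence is conditional. Bias needs a dropped factor whose distribution changes differently between the arms from baseline to the intervention period. That is possible, because different women deliver in each period and those in the intervention period enter after open allocation of their hospital, but the article neither shows nor excludes it. Under the assumed inputs, the interaction odds ratio moves from about 0.74 to 0.80–0.82, or to 0.70 in the other direction; with no differential shift it hardly moves (0.739 to 0.744). How many variables would be deleted, if any, is unknown. The change is worth making because it is cheap and the present rule has no stated advantage, not because material bias has been demonstrated.

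**What to change.** - Delete the exclusion of variables above 1% missing, and keep every prespecified covariate in the primary model.
- Handle missing covariate values by multiple imputation, with hospital, arm, period and outcome in the imputation model. Using this at all levels of missingness also closes the gap at exactly 1%.
- Say explicitly that the rule concerns adjustment variables.
- Report the model without the covariates above 1% missing as a sensitivity analysis, so that readers can see whether they matter.
- Carry the same set into the economic models, as the article already intends.

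A missing-value category is not a safe shortcut: the programme asks intervention hospitals to assess the nomogram items, so charting of those items could change by arm and period.

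The cost is a change of wording plus modest extra programming and analysis. No new data are needed.

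### The non-convergence fallback ignores hospitals and tests at P<0.001; that cut-off does not correct the standard errors and is not calibrated to the clustering

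*Protocol article*

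**What the plan says.** The protocol article, Statistical analysis, makes the odds ratio for the group-by-period interaction the main measure of effect. It is to be estimated by logistic GEE with an exchangeable working structure, reported with a 95% CI and tested at two-tailed 0.05. If the GEE models do not converge, the effect is to be estimated by a "multivariable logistic model, which do not account for within-hospital clustering; to correct for the resulting underestimation of the standard errors, a conservative" cut-off for P, set at 0.001. The sentence closes the paragraph on secondary outcomes and subgroups and is not limited to any one outcome. The section gives no other CI level or standard error for this case.

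Sample size and power calculation gives the figures against which the rule can be judged: "we assumed an intraclass correlation coefficient of 0.001"; "assuming a baseline rate of 4.5% for the three strata"; "we would have to enroll 40 hospitals in the study, with an expected total of 7360 women with one prior cesarean delivery per year", which over one baseline year and two intervention years makes 22,080; and the aim "to achieve a power of 80% to detect a 25% relative reduction with the intervention", "at a two-sided alpha significance level of 0.05".

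**The concern.** Clustering makes the naive standard error too small by a factor that depends on the ICC, the cluster size and how stable hospital effects are between periods. A fixed P cut-off responds to none of these. It leaves the estimate's standard error and interval uncorrected and moves only the decision line, by the same amount for every outcome. A numerical failure of the working correlation could then change the verdict on an outcome, at an error rate that nobody has chosen, beside an interval that does not match the test. A clustered analysis with the same point estimate remains available in that situation.

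**Working it through.** **Inputs (Sample size and power calculation).** 40 hospitals, 20 per arm; 7360 women a year, so 7360/40 = 184 per hospital-year; baseline 3680 per arm; two-year intervention period 7360 per arm (368 per hospital); 4.5% against 0.75 × 4.5% = 3.375%; ICC 0.001. My assumptions: equal hospital sizes, unadjusted rates, and a correlation of hospital effects between periods (call it c), which the article does not give and which I vary from 0 to 1.

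**1. The plan's own power.** Intervention-period comparison: design effect 1 + 367 × 0.001 = 1.367; effective n per arm 7360/1.367 = 5384; power at two-sided 0.05 is 85%. The stated 80% is therefore met on this basis, though not reproduced exactly.

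**2. What P<0.001 implies.** The critical values are 3.291 and 1.960. Ratio 3.291/1.960 = 1.68; squared, 2.82. The rule is equivalent to inflating every variance by 2.82. At 368 women per hospital that corresponds to an ICC of (2.82 − 1)/367 ≈ 0.005, five times the planning value.

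**3. Interaction, naive standard error.** Sum of 1/[n p(1 − p)] over the four cells: 0.00632 + 0.00632 + 0.00316 + 0.00417 = 0.01997; SE = 0.1413. Log OR = ln(0.741) = −0.299; z = 2.118.
- Power at 0.05: Φ(2.118 − 1.960) = 56%.
- Power at 0.001: Φ(2.118 − 3.291) = 12%.

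**4. Interaction, allowing for clustering at ICC 0.001.** With c = 1 hospital effects cancel and the design effect is about 1.00. With c = 0 the cell variances are multiplied by 1.183 (baseline) and 1.367 (intervention period): true SE = 0.158, and (0.158/0.1413)² = 1.25.

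| | c = 1 | c = 0 |
|---|---|---|
| Valid clustered test at 0.05, power | 56% | 47% |
| Fallback at 0.001, power | 12.1% | 14.7% |
| Fallback type I error | 0.10% | 0.33% |

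A simulation (4000 trials per setting, c = 0, 0.5, 0.8 and 1) gave fallback power of 12–16%.

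**5. Post-period comparison under the fallback.** Naive z = 0.01125/0.003205 = 3.51; √1.367 = 1.169. Power = Φ[(3.51 − 3.291)/1.169] = 57%, against 85% at 0.05. Type I error = 2[1 − Φ(3.291/1.169)] = 0.5%.

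**6. Larger ICC (an assumption outside the plan).** At ICC 0.01 and c = 0 the true SE of the interaction is 0.2646, or 1.872 times the naive value. Fallback type I error = 2[1 − Φ(3.291/1.872)] ≈ 8%.

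**7. Interval against verdict.** With SE 0.1413 the naive 95% CI excludes 1 when the OR is below exp(−1.960 × 0.1413) = 0.758, but P<0.001 requires an OR below exp(−3.291 × 0.1413) = 0.628. Between these values the two disagree, and the design OR of 0.741 lies there. At the planned effect the chance of landing there is 56.3% − 12.1% ≈ 44% by formula (41–46% in the simulation).

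**8. The alternative.** Independence GEE with hospital-clustered robust errors, a 20/19 variance factor and t with 38 df gave, in the same simulation, type I error of 4.7–5.4% and power of 47–55%.

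**The case against.** The strongest defence is that this is a contingency clause, openly prespecified as conservative, with sources cited that I cannot see. The primary model has 22,080 women and, at rates of 4.5% and 3.375%, roughly 910 to 990 events in 40 hospitals; nothing in the article suggests that an exchangeable GEE would fail there. That stands. The probability of using the fallback is unknown, and it is more plausible for rarer outcomes or subgroups than for the primary.

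Four stronger readings are tempting, and the article does not support them.
- That the trial has 12% power. The figure holds only for the interaction and only after non-convergence. Interaction power at 0.05 is already about 47–56%, so the distance from 80% is mostly a separate matter. A test with exactly 80% power at 0.05 would have 31% at 0.001.
- That the fallback is always too strict, or that the plan's ICC implies a design effect of 1.0 for the interaction. The latter needs hospital effects perfectly correlated between periods, which is not stated. No ICC is given for the secondary outcomes, and step 6 shows that the direction can reverse.
- That the protocol prescribes contradictory intervals. The 95% CI is described for the GEE analysis; what interval accompanies the fallback is not said. The conflict follows only if the same CI is carried over.
- That the plan misreports its error rate. The 0.001 threshold is disclosed; what is wrong is the claim that it corrects the standard errors.

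**Conclusion.** The point holds as a matter of calibration and should be changed, although it bites only if convergence fails. The cut-off stands in for a fixed design effect of 2.82, which the plan's own figures do not support: they give about 1.37 for the intervention-period comparison and 1.00 to 1.25 for the interaction. At the planning ICC the fallback discards most of the interaction's power, and at a larger ICC it may fail to protect the 5% level. These sizes rest on equal hospital sizes, unadjusted rates, the planning ICC (except where 0.01 is named) and the full range of between-period correlation.

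**What to change.** Replace the fallback sentence. If the exchangeable GEE does not converge, refit with an independence working correlation and hospital-clustered robust standard errors, with a small-sample correction (for example a degrees-of-freedom factor and a t reference with about 38 df). Keep the two-sided 0.05 level and report the matching 95% CI. The point estimates are those of ordinary logistic regression, and the fit converges whenever that model does.

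The cost is small but not nil: one sentence of wording, standard procedures in the SAS software already named, and the small-sample correction that 40 hospitals require. No data collection changes.
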